#### Secondary outcomes

Secondary outcome measures for abstinence include 7-day point prevalence abstinence measured at 8 months, biochemically confirmed by an exhaled CO of < 10 ppm. We will also measure 6-month prolonged abstinence using the Russell standard criteria, defined as smoking fewer than five cigarettes between 2- and 8-month follow-ups, confirmed by an anabasine concentration of < 1 ng/ml at 2 months and an exhaled CO concentration of < 10 ppm at 8 months (or anabasine concentration of < 1 ng/ml at 8 months if CO measurement unavailable). There is no funding for analysing all saliva samples at 8 months; therefore, we will verify abstinence using exhaled CO in the first instance.

As an additional measure of smoking reduction, we will assess the mean change in salivary anabasine concentrations from baseline to 2 months.

#### Other measures and exploratory outcomes

Baseline assessments are detailed in Table 1. Ethnic group will be classified using UK census 2015 categories. The researcher will collect a saliva sample and measure exhaled CO using a CO monitor as a measure of smoke intake. Severity of nicotine dependence will be measured using the six-item Fagerstrom Test for Cigarette Dependence (FTCD). The FTCD will be re-administered at 2- and 8-month follow-ups. We will assess motivation to stop smoking with the question “How likely are you to quit smoking within the next six months?” Responses will be measured on a five-point Likert scale from “Very unlikely” to “Very likely”.

Recruitment and follow-up outcomes will be measured by recording the number of people in the population of interest who respond to letters of invitation from the practices, the number of people who consent to enrolment into the study at baseline and the number of people who complete follow-up at 2 and 8 months after receiving the brief advice intervention.

GPs or nurses will record on the randomisation card whether an e-cigarette starter pack was accepted or declined by participants; this will be returned to the researcher after the consultation. Use of e-cigarettes will be assessed in a questionnaire administered at 2- and 8-month follow-ups. Questionnaire items include the total number of times the e-cigarette was used per day (i.e. ‘sessions’ not puffs), number of days using the e-cigarette, strength of nicotine e-liquid used and frequency of e-liquid purchased. Saliva samples collected at baseline and two-month follow-up will be analysed for cotinine, a measure of nicotine intake, arising from both e-cigarette and tobacco use. We are measuring cotinine to examine whether participants in the intervention group cut down or replace their nicotine intake with e-cigarette use.

We will also measure the number of people who tried to stop smoking, uptake and use of the NHS SSS and use of pharmacotherapy. Adverse event data will be recorded in the case report form (CRF) at 2- and 8-month follow-ups and at other points if researchers are made aware.

We will measure practitioner fidelity to the intervention using a study-specific behaviour checklist, which will be checked against audio recordings of the consultations after each session of annual review appointments. The checklist will assess whether the GP or practice nurse asked the participant about their smoking status, whether they gave brief smoking management and cessation advice, whether they offered a referral and carried out the consultation according to the correct group allocation (to assess contamination). We will draw on conversation analytic (CA) methods to inform this objective. Contamination will also be assessed in the post-consultation questionnaire, where all participants will be asked to report on whether e-cigarettes and other smoking cessation aids were mentioned during the consultation.

To measure acceptability of the intervention, we will examine participants’ views about the care they have received on their smoking in both arms by questionnaire immediately after the consultation and through semi-structured interviews with the intervention group only. Participants will be asked to rate how helpful and appropriate they found practitioners’ advice and support on smoking. They will also be asked about the quality of advice given via recall of key points of the consultation, which will be triangulated with audio recordings of the consultations. At 2 months, participants in the intervention arm will be asked whether they used the study-dedicated telephone support service, the practical support booklet and online video tutorials; they will rate each resource on a five-point Likert scale from “Very unhelpful” to “Very helpful”. We will assess attitudes towards e-cigarettes, cutting down and stopping smoking in a questionnaire administered at baseline and 2 months, as a measure of self-efficacy and outcome expectations.

Before intervention training begins and after all therapeutic visits have been completed at a practice, practitioners will be given a questionnaire about their attitudes regarding e-cigarettes as a tool for smoking cessation, as a measure of self-efficacy and outcome expectations. Practitioners and the vape team will be interviewed about their experiences of the programme after completing the trial, as described in the embedded qualitative study.

### Safety reporting

#### Adverse events

This is not a trial of an investigational medicinal product. E-cigarettes are a consumer product and the devices used in the trial are readily available to purchase in stores and online. For the purposes of the trial, we will record adverse events in the case report form by asking the participant to complete a symptoms checklist at the 2-month follow-up appointment. The checklist will contain symptoms commonly reported in previous studies on e-cigarettes [39], including throat/mouth irritation, cough, dry mouth, shortness of breath, headache, nausea, dizziness, stomach pain and palpitations. Participants will rate whether they have been troubled by any of these symptoms in the past 24 h, on a five-point Likert scale from “Not at all” to “Extremely”.

In this population, we expect that serious adverse events such as hospitalisation and death will occur during the 8 months of observation. The Cochrane review provides evidence that e-cigarettes do not cause serious adverse events but the data are sparse and imprecise [39]. As such, there are no expected serious related adverse events in this study. However, to provide further evidence on this, we will collect data on the occurrences of serious adverse events at each follow-up. We will assess each SAE in a blinded manner for relatedness to the intervention by the chief investigator (CI) for monitoring patient safety. For the purpose of trial reporting, however, we will convene an independent committee to make this judgement. Reports of related and unexpected SAEs (RUSAEs) will be reported to the REC within 15 working days of the chief investigator becoming aware of the event.

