#### Eight-month follow-up

The study team will contact all participants 6 months after their 2-month follow-up by telephone, text message or email to establish smoking status, number of cigarettes smoked per day, current pack/pouch size, use of pharmacotherapy, use of e-cigarettes and any serious adverse events (SAEs). Participants who declare abstinence will be invited to return to the practice or receive a home visit by a member of the study team for exhaled CO measurement to confirm this. Every effort will be made to contact participants exactly 6 months after the 2-month follow-up, before data are classed as lost to follow-up. If the participant is unable to provide a CO measurement to validate abstinence, a salivette will be posted to the participant with instructions on how to return the sample back to the study team. Again, if the participant reports that they have stopped smoking and they are taking a particular medication that requires a dose adjustment, the participant’s GP will be informed.

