### Statistics and analysis

#### Sample size

In order to correct the type 1 error rate for the fact that there are two primary outcomes we will be using the Holm-Bonferroni method of adjustment [59]. The smaller *P* value will be compared to an alpha of 0.025 (this will probably be for reduction in smoking) and if this is significant, the larger *P* value (which will probably be for cessation) will be compared to an alpha of 0.05. A total sample size of 320 will allow us to detect a risk ratio of 2.8 for the proportion of patients reducing their smoking and a risk ratio of 3.4 for the proportion of patients who stop smoking [38]. This assumes power of 90% and control group rates of 5% and 8% for stopping and reducing, respectively [38]. No allowance will be made for loss to follow up as all such cases will be assumed to have continued their baseline level of smoking.

We expect to see adherence to the behavioural intervention by practitioners of 70%, use of the e-cigarette at follow-up of 40%, and follow-up 70% of enrolled participants. We will be able to estimate these proportions with 95% confidence intervals being no greater than ±8% with a sample of 160 people in the intervention group and ±6% for the whole sample of 320 participants.

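### The only structured checklist for non-serious adverse events looks back 24 hours, once, at 2 months, so it does not cover earlier e-cigarette use, notably by people who stopped because of symptoms

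*Protocol article*

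**What the plan says.** The Adverse events section gives the method for recording adverse events: "asking the participant to complete a symptoms checklist at the 2-month follow-up appointment". The listed symptoms are those commonly reported with e-cigarettes, such as throat or mouth irritation, cough, nausea and palpitations. The recall period is fixed as well: "Participants will rate whether they have been troubled by any of these symptoms in the past 24" hours, on a five-point scale. Serious adverse events are handled separately and are collected at each follow-up.

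Three other places bear on this:

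- The Two-month follow-up section has the researcher record any adverse events, but gives no method or recall period. For people who cannot be seen in person, it lists only smoking behaviour and a posted saliva kit.
- Other measures and exploratory outcomes states: "Adverse event data will be recorded in the case report form (CRF) at 2- and 8-month follow-ups", and adds events that come to the researchers' attention at other times.
- The Eight-month follow-up list ends with "use of pharmacotherapy, use of e-cigarettes and any serious adverse events (SAEs" and does not mention non-serious events.

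On exposure, the starter pack is offered at the consultation, about two months before the checklist. It contains three bottles of e-liquid, and participants buy their own afterwards. The Sample size section expects "use of the e-cigarette at follow-up of 40%, and follow-up 70% of enrolled participants".

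**The concern.** For this device the recall window sits at the wrong end of the exposure period. Someone who had nausea or throat irritation in the first days of vaping, and gave up the device for that reason, can truthfully choose the lowest category for every symptom at 2 months. The gap is selective: those who tolerated the e-cigarette least are the least likely to be using it when asked.

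At stake is what the trial can say about tolerability. It enrols people with COPD, asthma, heart disease and serious mental illness, and acceptability is among its aims. A 2-month symptom score reported as adverse events during use would describe mainly those who carried on.

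**Working it through.** **Inputs.** Intervention arm 160 (Participant entry). Expected use 40% and expected follow-up 70% (Sample size). Checklist once, at 2 months, 24-hour window (Adverse events).

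**The plan's own figure.** The plan says 95% confidence intervals for its expected proportions will be no wider than ±8% with 160 people. For 40% use, 1.96 × √(0.40 × 0.60 / 160) = 0.076, or ±7.6%. The figure reproduces. It concerns precision only and does not bear on the recall window.

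**Non-users among those who complete the checklist.** Assume that everyone followed up completes it: 160 × 0.70 = 112.

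| How the 40% is read | Users among 112 | Non-users among 112 |
|---|---|---|
| 40% of those followed up | 112 × 0.40 = 44.8, about 45 | 67.2, about 67 (60%) |
| 40% of all 160, and every user attends | 160 × 0.40 = 64 | 112 − 64 = 48 (43%) |

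So about 43% to 60% of completers may not be users. Three things limit this range:

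- The 40% and 70% are not tied to the 2-month visit.
- Under Other analyses, continued use means use until smoking stopped, or use on more than half of days. That is not use in the last 24 hours. A person below the threshold may have vaped yesterday, and a person counted as a continued user may have stopped vaping after quitting.
- Non-users include people who declined the starter pack and have no device symptoms to report. No expected uptake is given, so the number who tried and stopped cannot be derived.

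**Length of the window.** One day in about 61 is 1/61 = 1.6% of the period since randomisation. This is a share of time, not of symptoms: a persistent or recurring symptom will appear in a 24-hour rating.

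**Do the other routes cover earlier use?**

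| Route | Non-serious events? | Systematic, both arms? | Recall period |
|---|---|---|---|
| Checklist | Yes | As described, yes | 24 hours |
| Any adverse events at 2 months | Yes | No separate method given | Not stated |
| Recording when researchers become aware | Possibly | No, passive | None |
| Serious adverse events at each follow-up | No | Yes | Not limited to 24 hours |
| Vape team calls | Not their purpose | Pack acceptors only | None |
| Qualitative interviews | Possibly | Up to 40 intervention participants | Not stated |

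None of these is described as eliciting non-serious events since the consultation, systematically, in both arms.

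**The case against.** The strongest reply is that the checklist is a valid measure of something else. By randomised arm, it gives current symptoms at 2 months with little recall error. The article states no between-arm test of symptoms, does not list safety among its objectives, and calls the trial low risk. It is also a condensed article: the visit schedule figure and the case report form are not shown, and the researcher's record of any adverse events at 2 months carries no 24-hour limit. That stands as far as it goes. Early events may be picked up by that route, but the only method the article describes is the checklist.

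Three stronger readings are tempting and are not supported:

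- A reader might infer that the plan expects 60% of the arm, 96 of 160, to have stopped vaping by 2 months, so that symptoms are largely missed. The 40% has no time point, the 96 would include people who never took the device, and nothing in the documents gives the proportion of symptoms missed.
- A reader might infer that a planned comparison is biased towards no difference. No such comparison is stated. The risk arises only if the checklist is used or described as events during use.
- A reader might see a contradiction between adverse event data at 8 months in one section and only serious events in the other. Serious events are adverse event data, so the two can be read together. What is left is unclear wording.

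The objection on timing also stands. Recruitment ran from June 2018 to May 2019, with 243 recruited by 1 April 2019, and the article rests on protocol version 3.0 of 21 May 2019. Many 2-month visits were already past.

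**Conclusion.** The point holds as a limit of the instrument. The one structured tool described for non-serious events measures symptoms present at 2 months. It does not cover earlier use, and it is least suited to participants who tried the e-cigarette and stopped because of symptoms.

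Its size can be given only as a range for who is asked: roughly 43% to 60% of intervention checklist completers may not be users at that time. This assumes that the 40% and 70% apply at 2 months and that everyone followed up completes the checklist. It is not an estimate of symptoms missed, which the documents do not allow. The finding is a cheap improvement to safety information. It does not affect the primary outcomes.

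**What to change.** 1. Keep the checklist and its 24-hour rating. For each symptom add, in both arms, whether it occurred *at any time since your annual review consultation*. For those who took the starter pack, add whether it led them to stop or cut down the e-cigarette.
2. Use the same items in 2-month follow-ups by telephone, text or email.
3. Where the 2-month visit has passed, ask the added items at the 8-month contact. This works only where that contact is still to come. At 21 May 2019 it would exclude people randomised before about 21 September 2018, eight months earlier. Otherwise, report the checklist as symptom prevalence at 2 months, not as adverse events during use.
4. State in the same terms, across Two-month follow-up, Eight-month follow-up, Other measures and exploratory outcomes, and Adverse events, which non-serious events are elicited, when, and over what period.

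**Cost.** One column on an existing questionnaire and a wording amendment. Recall over two months is less precise than over a day, and longer recall at 8 months less so again, which is why the 24-hour rating stays. Introduced mid-trial, the change leaves two versions of the instrument. The report should say how many participants answered each, by arm.

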### Trial closure

The end of study is the date of the last debrief of the last participant following the 8-month follow-up.

### Statistics and analysis

#### Sample size

In order to correct the type 1 error rate for the fact that there are two primary outcomes we will be using the Holm-Bonferroni method of adjustment [59]. The smaller *P* value will be compared to an alpha of 0.025 (this will probably be for reduction in smoking) and if this is significant, the larger *P* value (which will probably be for cessation) will be compared to an alpha of 0.05. A total sample size of 320 will allow us to detect a risk ratio of 2.8 for the proportion of patients reducing their smoking and a risk ratio of 3.4 for the proportion of patients who stop smoking [38]. This assumes power of 90% and control group rates of 5% and 8% for stopping and reducing, respectively [38]. No allowance will be made for loss to follow up as all such cases will be assumed to have continued their baseline level of smoking.

We expect to see adherence to the behavioural intervention by practitioners of 70%, use of the e-cigarette at follow-up of 40%, and follow-up 70% of enrolled participants. We will be able to estimate these proportions with 95% confidence intervals being no greater than ±8% with a sample of 160 people in the intervention group and ±6% for the whole sample of 320 participants.

### Analysis plan

#### Primary and secondary analyses

The proportion of participants who reduce smoking in each group will be presented. A log-binomial regression model will be applied to the data and the treatment effect will be reported as a relative risk and 95% confidence interval, adjusted for GP practice. A similar procedure will be used to analyse the proportion of participants who abstain from smoking. Analyses will be carried out on an intention-to-treat basis, according to the Russell Standard [60], where participants lost-to-follow up are assumed to be smokers or not to have reduced and we will impute missing anabasine concentrations with the baseline value.

The mean (SD) change in salivary anabasine from baseline to 2 months will be reported for each group and the difference and 95% CI will be computed using linear regression with adjustment for GP practice. Assumptions of linear regression will be assessed and if violated a Mann-Whitney test will be adopted and the median (IQR) will be used to summarise the data and difference in medians (95% CI) will be reported.

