## Background

Although smoking has more than halved since the 1970s, 14.7% of adults in the UK still smoke [1], costing the National Health Service (NHS) £2.5 billion a year from treating smoking-related chronic diseases [2]. Reducing smoking remains a key public health priority, particularly among those with smoking-related chronic diseases and serious mental illnesses (SMI), as their health can improve if they stop smoking or decline if they continue. In people with chronic obstructive pulmonary disease (COPD) continued smoking increases the risk of hospitalisation and chest infections and stopping smoking is the only intervention known to decrease the rate of decline in lung function [3, 4]. In hypertension, diabetes and chronic kidney disease, continued smoking leads to more rapid progression of renal disease [5–7]. In asthma, smoking cessation improves symptom control and can decrease the need for medication [8, 9]. In ischaemic heart disease, smoking cessation reduces recurrence by a third, more than any other therapeutic intervention [10]. Stopping smoking is associated with reduced anxiety and stress among people with mental health conditions [11]. Overall, quitting reduces mortality, even in people with smoking-related morbidity [12, 13]. Although almost everyone with a serious smoking-related disease tries to stop smoking on diagnosis [14], relapse is common, with evidence that most smokers continue smoking [15].

People with smoking-related conditions are often called ‘hardcore smokers’ because they have often tried and failed to stop smoking, despite trying most available means [16]. Similarly, smokers with SMI are often defined as hardcore smokers as they tend to smoke more heavily and find it more difficult to quit than those without SMI [17]. Primary care practitioners are well-placed to support these groups in stopping smoking and this is encouraged in general practices in the UK through a ‘pay for performance’ contract called the Quality and Outcomes Framework (QOF) [18]. The QOF rewards GPs for providing quality care for people with smoking-related illnesses and SMI. Since inception, GPs have had to offer advice on smoking, and since 2012, they offer referral for support and pharmacotherapy annually to people with smoking-related conditions and with serious mental health disorders. While the QOF has improved rates of recording advice and referrals [19], some smokers are still less likely to receive help in quitting [20].

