### Participant entry

A total of 320 participants will be recruited into the trial: 160 participants in each of the two treatment arms. See Fig. 1 for the planned flow of participants through the trial and Additional file 2 for the SPIRIT checklist.

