### Recruitment

Recruitment centres at the Universities of Oxford and Nottingham (United Kingdom) will recruit through GP practices. General practice teams review patients with chronic diseases at least annually, which includes enquiry about smoking status and, for smokers, offer of help to quit smoking. Around 20–30 GP practices will search their patient databases for all current smokers with one or more chronic conditions who are due to have an annual review in the new QOF year, beginning in April 2018. GPs will screen the search list to ensure that all those identified are medically appropriate to participate in the trial. Practice staff will write to or send a text message to these patients inviting them to take part. Patients who are interested in taking part will contact the study team by telephone, text message, email or return reply slip.

The study team will carry out preliminary screening and if the patient appears to be eligible, s/he will be asked to attend a baseline assessment at their GP practice to confirm eligibility (see Additional file 3 for enrolment process). A participant information sheet (PIS; see Additional file 4) and baseline appointment confirmation letter will be sent to potential participants.

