### Randomisation and blinding

Participants will be randomised to intervention or control with a 1:1 allocation ratio. A randomisation list will be generated by the trial statistician using the current version of Stata and validated by a second statistician within the Primary Care Clinical Trials Unit (PC-CTU). The randomisation will be stratified by practice and will use varying block sizes to ensure allocation concealment. The randomisation list will then be passed to someone independent of the trial who will create the randomisation envelopes.

Practitioners will randomise patients during the annual review appointment. On the day of the annual review session, a researcher will give each practitioner a set of opaque A5 sealed envelopes, which will contain a colour-coded randomisation card. The envelopes will be numbered in sequence. The GP or practice nurse will only open the randomisation envelope after they have delivered usual care advice on smoking and are satisfied that the patient meets eligibility for the trial, i.e. the patient confirms that s/he is currently a smoker and declines usual care treatment for stopping smoking. The patient is classed as enrolled in the trial only after the randomisation envelope has been opened. The randomisation card inside the sealed envelope will reveal the patient’s treatment allocation to the GP or nurse, but not the patient. The randomisation envelope will be returned to the researcher by the patient after their consultation.

If the patient is no longer a smoker or accepts usual care treatment, practitioners will fill in a patient ineligibility card containing a tick box option to select if they did not randomise and enrol the patient into the trial. The tick box will indicate the reason for non-enrolment, i.e. patient has stopped smoking, patient accepted usual care or any other reason where it is deemed clinically inappropriate. The ineligibility card will be returned to the researcher after the session and the patient will be thanked for their time given to the study and debriefed.

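### The primary models adjust only for GP practice: valid as planned, but baseline FTCD is already collected and could be pre-specified as a covariate for a small gain in precision

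*Protocol article*

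**What the plan says.** **Model.** Under Primary and secondary analyses, the protocol article fixes a log-binomial regression for the reduction outcome: "the treatment effect will be reported as a relative risk and 95% confidence interval, adjusted for GP practice". For abstinence it says "A similar procedure will be used to analyse the proportion of participants who abstain from smoking". No other covariate is named for either outcome.

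**Design.** Under Randomisation and blinding: "The randomisation will be stratified by practice and will use varying block sizes to ensure allocation concealment". No baseline smoking variable is used in the allocation. Under Recruitment, "Around 20–30 GP practices will search their patient databases"; under Participant entry, there are "160 participants in each of the two treatment arms".

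**Baseline data.** Table 1 lists cigarettes per day, nicotine dependence and a saliva sample for anabasine at the baseline visit. That visit comes before the consultation at which the envelope is opened. Under Other measures and exploratory outcomes, "Severity of nicotine dependence will be measured using the six-item Fagerstrom Test for Cigarette Dependence (FTCD".

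**Endpoint.** Under Primary outcomes, reduction requires at least a halving of daily cigarettes against the person's own baseline, and salivary anabasine below the baseline value.

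**The concern.** The trial pays for a dependence score on everyone before randomisation, does not balance on it, and then does not use it in the primary models. If dependence predicts stopping or cutting down, two things are given up. Some outcome variation that could be explained remains in the standard error. And if the arms happen to differ in dependence, that difference passes into the reported relative risk.

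With few events expected, one realised imbalance could be visible in the result. A covariate chosen after the imbalance has been seen would carry little weight with readers. Under Trial status, recruitment is reported as finished and follow-up as under way, so the time for naming covariates credibly is limited.

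**Working it through.** **1. The plan's own figure.** Inputs from Sample size: control rates 5% (stopping) and 8% (reducing), risk ratios 3.4 and 2.8, 90% power, 160 per arm. The smaller P value "will be compared to an alpha of 0.025 (this will probably be for reduction in smoking", and the larger is compared with 0.05. Sidedness is not stated; two-sided is assumed.

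- Intervention rates: 0.05 × 3.4 = 0.17 and 0.08 × 2.8 = 0.224.
- Power = Φ{[(p₁ − p₀)√160 − z√(2p̄(1 − p̄))] / √(p₀(1 − p₀) + p₁(1 − p₁))}.
- Stopping: 88.7% at 0.025 and 93.3% at 0.05.
- Reducing: 91.5% at 0.025.

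The stated 90% is reproduced to within 2 points at 0.025 with no covariate, so the planned power does not depend on adjustment.

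**2. Events and model size.** Stopping: 160 × 0.05 + 160 × 0.17 = 35.2. Reducing: 160 × 0.08 + 160 × 0.224 = 48.6. With practice as fixed effects, 20–30 practices already use 19–29 parameters. The expected number of practices without an event is K(1 − p̄)^(320/K), with p̄ = 0.11 or 0.152 and equal practice sizes assumed:

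| | K = 20 | K = 30 |
|---|---|---|
| Stopping | 3.1 | 8.7 |
| Reducing | 1.4 | 5.2 |

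**3. Precision.** The article gives no prognostic strength, so a baseline score with SD 0.4, 0.6, 0.8 or 1.0 on the logit scale is assumed. Trials were simulated at 160 per arm. The analysis was logistic regression with standardisation to the marginal relative risk, with a very small penalty for practices without events. The table gives the variance of the log relative risk with covariate plus practice, divided by that with practice only:

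| Setting | SD 0.4 | 0.6 | 0.8 | 1.0 |
|---|---|---|---|---|
| Stopping, 20 practices, 2,000 trials | 0.987 | 0.989 | 0.984 | 0.962 |
| Stopping, 25 practices, 1,000 trials | 1.01 | 1.01 | 0.98 | 0.95 |
| Reducing, 20 practices, 2,000 trials | 0.995 | 0.977 | 0.958 | 0.929 |
| Reducing, 25 practices, 1,000 trials | 0.99 | 1.00 | 0.95 | 0.93 |

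The gain is about nil at the weak end and up to 7% at the strong end. At most this equals 0.07 × 320 ≈ 22 participants. One further useless covariate in the reduction model costs about one percentage point of variance or less (ratios 0.997, 0.979, 0.967, 0.938).

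A harsher test used modified Poisson models with 20 practice terms and three covariates, two of them noise. It gave variance ratios of 0.98–1.03, and power gains of 0.2–0.3 points (stopping) and 0.6–1.5 points (reducing).

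**4. Chance imbalance.** The SD of the difference in mean standardised score between arms is √(2/160) = 0.112. So P(|difference| > 0.2 SD) = 2[1 − Φ(0.2/0.112)] = 0.074. This assumes that practice stratification does not itself balance the score.

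- An imbalance of 0.2 SD moves the log odds ratio by 0.2 × 0.4 = 0.08 to 0.2 × 0.8 = 0.16, a factor of 1.08–1.17. The shift in the log relative risk is somewhat smaller.
- SE of the log relative risk = √[(1 − p₀)/(160p₀) + (1 − p₁)/(160p₁)] = 0.39 (stopping) and 0.31 (reducing).
- The shift is therefore about 0.2–0.5 SE.

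In simulated trials with practice terms where imbalance favoured the intervention by more than 0.2 SD (3–4% of trials), the practice-only relative risk for reduction averaged 8%, 9%, 18% and 21% too high across the four SDs. After adjustment the error was −3% to +1%, with simulation error of roughly 4 points.

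**The case against.** The strongest reply is that nothing here is wrong. The model adjusts for the factor used in the randomisation, the type I error holds, the planned power needs no covariate, and the confidence interval already allows for chance imbalance. All of that stands. A reader might infer that the practice-only estimate is biased or the trial underpowered; the article supports neither.

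A reader might also infer that the plan ignores baseline consumption and anabasine. For reduction it does not: both are built into the endpoint definition, although not as model covariates. Regression to the mean from a high baseline reading acts alike in both arms under randomisation.

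Nor does the Background establish that dependence predicts the outcome here. Its remark about smokers with SMI, that "they tend to smoke more heavily and find it more difficult to quit than those without SMI", describes two features of a subgroup. It is not a link between FTCD and stopping or reducing in this trial.

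The model is also already crowded: 19–29 possible practice parameters against 35–49 events, with several practices likely to have no abstainer. That is a fair warning against simply adding terms to a log-binomial fit, and the fix has to deal with it.

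Finally, the statistical analysis plan was not available and may already contain adjusted analyses. What survives is narrow: the article states the adjustment set, and that set leaves out a measured baseline variable that could be added at little cost.

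**Conclusion.** The plan is valid as written. Adjusting only for GP practice forgoes a small potential gain and leaves any chance imbalance in dependence in the estimate. With practice terms kept, the variance of the log relative risk would fall by about 0–7%, and power would rise by at most about 1–2 points. Both figures assume a covariate SD of 0.4–1.0 on the logit scale, which the article neither gives nor supports with data.

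The better argument is protection in the single trial that will be reported: an imbalance above 0.2 SD has about a 7% chance and would move the estimate by roughly 0.2–0.5 SE. This is an optional efficiency improvement of low severity.

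**What to change.** Before unblinded data are seen, name baseline FTCD as one added covariate beside GP practice in both primary models. For reduction, log baseline anabasine may be added as well, with a simple rule for missing baseline samples, since the article itself expects some to hold too little saliva.

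Keep the marginal relative risk with 95% CI as the effect measure, for example by logistic regression standardised over the trial sample. State how practices without events are handled, for example by a random practice effect or light penalisation. Report the practice-only estimate beside the adjusted one. If the statistical analysis plan already names covariates, align the two texts instead.

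**Cost:** one or two more model terms with about 35–49 expected events, a departure from the stated log-binomial fit if the logistic route is taken, a sentence or two of wording and a few lines of code. No new data are needed.
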